**Characteristics of human subjects**

**Inclusion Criteria**

1. Men and women aged 50 to 86 years;
2. Able to fully comprehend and sign an informed consent form;
3. Diagnosis of stroke/TIA prior to study entrance and evidence of ischemic infarct and/or lacunar infarcts on MRI (defined as sharply demarcated hypointense lesions <20mm on T1-weighted images with corresponding hypointense lesions with hyperintense rim on FLAIR) and/or deep Cerebral Microbleeds (CMB) (defined as round hypointense lesions on T2-weighted gradient echo-images with a diameter < 10 mm in neuroimaging.
4. Meet Diagnostic and Statistical Manual of Mental Disorders – Fifth Edition (DSM-5) diagnostic criteria for major depressive episode that developed up to 12 months after the documented stroke/TIA.
5. Able to comply with scheduled visits, treatment plan, and other trial procedures;
6. Treatment with other antidepressants is allowed but subjects will be asked not to change their regular treatment regime during the trial.

**Exclusion Criteria:**

1. Hemorrhages and cerebral edema (e.g., subarachnoid haemorrhage, intracerebral hemorrhage, subdural hematoma, epidural hematoma)
2. Patients in a state of coma or with severe disturbance of consciousness, aphasia, agnosia, or deafness that subsequently affects expression and communication.
3. Significant acute medical illness including: drug overdose, severely disturbed liver, kidney or lung function, anemia, hypothyroidism, or uncontrolled diabetes.
4. Significant acute neurologic illness including: impaired consciousness, Parkinson's disease, Huntington's chorea, progressive supranuclear paralysis, brain tumor, subdural hematoma, multiple sclerosis, hydrocephalus, Binswanger's disease, or severe aphasia
5. Patients diagnosed with dementia or major neurocognitive disorder as defined by DSM-5at screening, or other neurological conditions that might dominate the clinical picture (multiple sclerosis, Parkinson's disease, epilepsy, Huntington's chorea, progressive supranuclear paralysis, brain tumor, subdural hematoma, multiple sclerosis, hydrocephalus, Binswanger's disease, etc.)
6. Subject has a history of human immunodeficiency virus (HIV), hepatitis B surface antigen (HBsAg) or hepatitis C antibody (anti-HCV) positive, or other clinically active liver disease, or elevated hepatic transaminases or bilirubin, or tests positive for HIV at Screening.
7. History of renal insufficiency or serum creatinine over 1.6;
8. Subject has a current or past diagnosis of bipolar or related disorders, intellectual disability, cluster B personality disorder (e.g., borderline personality disorder, antisocial personality disorder, histrionic personality disorder, and narcissistic personality disorder), psychotic disorder, schizophrenia, PTSD , and substance/alcohol use disorders other than nicotine in the past year (including barbiturates, methadone, opiates, cocaine, cannabinoids, and amphetamine/ methamphetamine).
9. Subject has suicidal ideation with intent to act during the screening phase or on Day 1 per investigator’s clinical judgment, or has a history of suicidal behavior within the past year; or subject has homicidal ideation/intent at Screening or on Day 1.
10. Subject has a history of malignancy within 5 years before screening (exceptions are squamous and basal cell carcinomas of the skin and carcinoma in situ of the cervix, or malignancy that in the opinion of the investigator is considered cured with minimal risk of recurrence).
11. Subject has known allergies, hypersensitivity, intolerance, or contraindication to Maraviroc or its excipients.
12. Subject has received an investigational drug (including investigational vaccines) or used an invasive investigational medical device within 60 days before the planned first dose of study drug or is currently enrolled in an investigational study.
13. Subject is a woman who is pregnant, breast-feeding, or planning to become pregnant while enrolled in this study or within 3 months after the last dose of study drug.
14. Subject has any condition for which, in the opinion of the investigator, participation would not be in the best interest of the subject (e.g., compromise the well-being) or that could prevent, limit, or confound the protocol-specified assessments.
15. Subject has had major surgery, (e.g., requiring general anesthesia) within 2 weeks before screening, or will not have fully recovered from surgery, or has surgery planned during the time the subject is expected to participate in the study.
16. Use of drugs with possible interactions with Maraviroc.

**Prohibitions and Restrictions**

- Potent CYP3A4 inhibitors are not permitted within 1 week or within a period less than 5 times the drug’s half-life, whichever is longer, before the first dose of study medication and throughout the study.
- Potent CYP3A4 inducers are not permitted for 30 days prior to the first dose of study medication and throughout the study.

Safety Evaluations

Physical examination, body weight, vital signs, 12-lead ECG, clinical laboratory tests, and evaluation of adverse events and concomitant therapies will be performed throughout the study to monitor subject safety. Suicidal ideation and behavior will be assessed by a psychiatrist, as well as continuous follow-up of mental state and adverse events after cessation of Maraviroc treatment.

Primary Efficacy Measures:

**MADRS** -The 10-item clinician-administered MADRS was designed to be used in subjects with MDD to measure the overall severity of depressive symptoms (Montgomery and Asberg 1979). The MADRS has been validated, is reliable, and is acceptable to regulatory health authorities as a primary scale to determine efficacy in major depression. The structured interview guide for the Montgomery Asberg Depression Rating Scale (SIGMA) will be used for each administration (Williams 2008). Using structured interview guides have previously been shown to increase the reliability of given scales. In depression, ‘response’ is commonly defined as a ≥50% reduction in the initial symptom score and remission is typically defined as a total score of ≤10 (Montgomery 1994). The primary efficacy evaluation will be the change from baseline in the MADRS total score in the treatment phase.

Secondary Efficacy measures:

**QIDS-SR16** - The patient administered 16-item quick inventory of depressive symptoms- self report (QIDS-SR16) is designed to be used in patients with MDD to measure the overall severity of depressive symptoms (Rush 2003; Trivedi 2004).

**CGI-I and CGI-S** - The clinical global impression – improvement (CGI-I) is a 7 point scale that requires the [clinician](https://en.wikipedia.org/wiki/Clinician) to assess how much the patient's illness has improved or worsened relative to a baseline state at the beginning of the intervention; The clinical global impression – severity (CGI-S) evaluates the severity of psychopathology from 1 to 7, and will provide an overall clinician-determined summary measure that takes into account all available information, including knowledge of the subject’s history, psychosocial circumstances, symptoms, behavior, and the impact of the symptoms on the subject’s ability to function (Guy 1976).

**GAD-7** - The 7-item patient-reported generalized anxiety disorder 7-item scale (GAD-7) is a brief and valid measure of overall anxiety (Spitzer 2006). Each item is rated on a 4-point scale (0 to 3), with the total score range from 0-21 (higher scores indicating more anxiety).

**GDS** – Geriatric depression scale, that has been has been tested and used extensively with older populations.

**PGI-S and PGI-C** - Patient Global Impression scales are commonly used measures of symptom severity, treatment response and the efficacy of treatments. The patient global impression - severity (PGI-S) will provide an overall patient-rated summary measure that assesses the severity of the subject’s MDD. The patient global impression of change (PGI-C) will provide an overall patient-rated summary that assesses subject perception of change in their MDD since starting study treatment (Rush 2005).

.

**MoCA** - Montreal Cognitive Assessment.

**SIS** - stroke impact scale.

**ADL** - the activities of daily living score.

**RNL** - Reintegration to Normal Living Index.

**Overview of Study Design**

This is a proof-of-concept, open-label, single center study conducted in 10 male and female adult subjects with PSD. Each subject will participate in 3 phases: (1) a screening phase of up to 1 week, (2) an open-label treatment phase of 10 weeks, and (3) an 8-week post-treatment (follow up) phase. The end of study will occur when the last subject in the trial completes his/her last study assessment.

Screening and Baseline assessments

After giving informed consent, subjects will be screened to determine eligibility for study participation. Note: Subjects who are not currently taking an antidepressant at screening are eligible to participate in this study (i.e., subjects may participate in the study whether or not they are taking an antidepressant). Subjects who are taking an antidepressant at the screening visit must have been receiving a stable dose (i.e., dose has been unchanged for at least 2 months before the screening visit) and will be guided to continue the antidepressant at the same dose during the treatment phase. All adverse events and special reporting situations, whether serious or non-serious, will be reported from the time a signed and dated informed consent form (ICF) is obtained until completion of the subject's last study-related procedure (which may include contact for follow-up of safety). If a subject withdraws before the end of the treatment phase for reasons other than withdrawal of consent, the early termination visit should be conducted at the time of discontinuation, followed by completion of the posttreatment phase. All subjects will self-administer the study medication.

**Recruitment and retention plans**

Screening and patient evaluation:

Participants will be out-patients referred from the community or the hospital’s ambulatory services, who meet entrance and exclusion criteria. After receiving a detailed explanation and signing informed consent, the participant will be further screened. All identifying information of participants will be saved in a separate password protected study log available only to study investigators. All the gathered data will be de-identified and coded with a pre-assigned study ID.

Eligible patients enrolled in the study will undergo a baseline visit (Week 1), in which they will receive the study drug following completion of all relevant assessments. During the first administration, participants will remain under clinical supervision and vital signs monitoring for 2 h at the Tel Aviv Sourasky Medical Center. Blood pressure and heart rate will be recorded before discharge. Patients will be evaluated every 2 weeks during the trial using multiple depressive, anxiety and functional questionnaires as well as cognitive tests. A final safety and efficacy assessment will be held 8 weeks after the patient’s last dose (Week 18).

Open-label treatment period:

On Day 1, subjects will start the study drug. A 1-week supply of capsules will be handed to participants after the consent has been signed, and baseline measurements obtained, usually on the same day. The second 2-weeks supply will be provided during a scheduled interim measurement assessment at TLVMC near the end of the 2nd week on medication. Participants will take Maraviroc 300 mg at 6-8AM. The capsules will be supplied by the hospital pharmacies and used under IRB approval as required.

The efficacy, safety, and biomarker evaluations that will be performed at each visit of the treatment phase and are described in the Time and Event Schedule.

Post-treatment phase

The efficacy and safety evaluations that will be performed at each visit during the post-treatment phase are described in the Time and Event Schedule.

All subjects who receive at least 1 dose of study medication should have 2 follow up visits conducted at 4 and 8 weeks after the last dose of study medication. The follow up visits at weeks 3, 5, 8, 9 will be telephone contacts. The follow up visit at 4 and 8 weeks after the last dose of study medication are clinic visits. Any clinically significant abnormalities persisting at the end of the study will be followed by the investigator until resolution or until a clinically stable endpoint is reached. All adverse events and special reporting situations, whether serious or non-serious, will be reported until completion of the subject's last study-related procedure (which may include contact for follow-up of safety).

TIME AND EVENTS SCHEDULE (Table S1)

| **Week 14 (4 weeks after last dose, Week 18 (8 weeks after last dose)** | **Telephone contact (week 3, 5, 8, 9)** | **week 4, week 7, week 10** | **Week 2** | **Day 1 (can be the same as screening)** | **Screening** | **Participant Assessment** |
| --- | --- | --- | --- | --- | --- | --- |
|  |  |  |  |  | **X** | Informed consent |
|  |  |  |  |  | **X** | Inclusion / Exclusion criteria |
|  |  |  |  |  | **X** | Medical history, demographics |
|  |  | **X** | **X** | **X** |  | Study Drug Administration |
|  |  |  |  |  |  | Safety Assessments |
| **X** |  | **X** | **X** | **X** | **X** | Physical examination |
|  |  | **X** | **X** | **X** | **X** | Body weight |
|  |  | **X** | **X** | **X** | **X** | Vital signs |
|  |  | **X** | **X** | **X** | **X** | 12-lead ECG |
|  |  |  |  |  | **X** | Carotid Doppler |
|  |  |  |  |  |  | Clinical Laboratory assessments |
|  |  | **X** | **X** |  | **X** | Hematology, Chemistry |
|  |  | **X** | **X** |  | **X** | Serum cytokines |
|  |  |  |  |  |  | Efficacy assessments |
| **X** |  | **X** | **X** | **X** | **X** | MADRS (7-day recall) |
| **X** |  |  |  | **X** |  | GDS |
|  |  | **X** | **X** | **X** | **X** | CGI-I + CGI-S |
| **X** |  | **X** | **X** | **X** | **X** | QIDS-SR16 |
|  |  | **X** | **X** | **X** | **X** | PGI-S |
| **X** |  | **X** | **X** | **X** | **X** | PGI-C |
| **X**  (for suspected Dementia) |  |  |  |  | **X** | GAD-7 (7-day recall) |
| **X** |  | **X (week 10)** |  |  | **X** | MoCA |
| **X** |  | **X (week 10)** |  | **X** |  | Computerized cognitive test battery (Neurotrax) |
| **X** |  |  |  | **X** |  | SIS |
| **X** |  | **X** |  | **X** |  | ADL |
| **X** |  |  |  | **X** |  | RNL |
|  |  |  |  |  |  | Ongoing Subject Review |
| **X** | **X** | **X** | **X** | **X** |  | Concomitant therapy^2^ |
| **X** | **X** | **X** | **X** | **X** |  | Adverse events^3^ |

^1^Visit window: Day 15 (+/- 1 day), Day 29, 43, 57 and 71 can occur +/- 3 days.

^2^Concomitant therapies must be recorded throughout the study beginning with signing of the informed consent until the last follow up visit.

^3^All adverse events and special reporting situations, whether serious or non-serious, will be reported from the time a signed and dated informed consent form is obtained until completion of the subject's last study-related procedure (which may include contact for follow-up of safety.

Abbreviations: **ADL** = the activities of daily living; **CGI-I =** clinical global impression – improvement; **CGI-S** = Clinical Global Impression – Severity (S); **ECG** = electrocardiogram; **GAD-7** = Generalized Anxiety Disorder 7-item scale; **GDS =** Geriatric depression scale; **MADRS** = Montgomery Asberg Depression Rating Scale; **MoCA** = Montreal Cognitive Assessment**; PGI-C** = Patient Global Impression of Change; **PGI-S** = Patient Global Impression – Severity; **RNL** = Reintegration to Normal Living Index; **SIS** = stroke impact scale (SIS).

**QIDS-SR16** = 16-item Quick Inventory of Depressive Symptoms- Self Report.

Laboratory work up: Blood samples for: cell blood count, lipids profile, liver and kidney function, inflammatory markers: highly sensitive c-reactive protein (hs-CRP), tumor necrosis factor (TNF)-alpha, interleukin-6 (IL-6), IL-10, IL-1 β, IL-2, IL-17A. Cytokine level will be determined using ELISA (R&D Systems, USA) and ProcartaPlex™ Multiplex Immunoassay (Affymtrix eBioscience) at the research laboratory for Stroke and dementia, Tel Aviv Sourasky Medical Center.

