# Toxicology

Maraviroc is the only CCR5 antagonist currently approved by the FDA, the European Commission and the Health Canada for treatment of patients infected with R5-tropic HIV-1. The drug is a small molecule metabolized by CYP3A4, with a good pharmacokinetic profile, relatively low protein binding and high bioavailability when given at standard doses twice a day. Maraviroc appears to be well tolerated, but the dose has to be adjusted when given with CYP3A4 inducers or inhibitors, primarily drugs that are also used for HIV therapy, but also for several anticonvulsants. Patients who take these medications will be excluded from the proposed trial. The drug should be used cautiously in patients with a history of orthostatic hypotension and patients with pre-existing liver dysfunction or co-infection with hepatitis B or C (these patients will also be excluded from the proposed trial). Maraviroc does not appear to cause clinically significant changes in concentrations of other medications. It is moderately lipophilic, so it can penetrate the blood-brain barrier. At a single dose of 150 mg or 300 mg, time to maximum concentration occurred by 2 hours post-treatment in humans. The terminal half-life is 14-18 hours, so a single dose used in the proposed protocol should be adequate, rather than the twice-daily (BID) treatment for AIDS.

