**Absorption**: The absorption of Maraviroc is highly variable with multiple peaks. The mean Tmax was between 2 and 3 hours with individual values ranging from 0.5 to 8 hours (with food). The absolute bioavailability for Maraviroc was 23% at 100 mg, and it has a predicted bioavailability of 31% at 300 mg. The absorption of Maraviroc is dose dependent, likely attributed to saturated efflux transporters in the intestine. Maraviroc is highly soluble in aqueous media across pH 1–7.5, has an efflux ratio >10 in Caco-2 cell monolayers and is a substrate for P-gp and the multidrug resistance protein.

**Bioequivalence:** The commercial tablet formulations (150 mg, 300 mg) are completely dissolved within 30 minutes (>90% within 15 minutes), and hence, dissolution will not be rate limiting for the absorption of Maraviroc. Bioequivalence was shown between the commercial 300 mg tablet and research formulation (2 x 150 mg). The solution had a 12% higher bioavailability than the research tablet.

**Metabolism**: The metabolism of Maraviroc was evaluated in 3 healthy male subjects after administration of 300 mg 14C Maraviroc as an oral solution in a fasted state. Whole blood samples and plasma samples were collected on days 1 to 6 at specified times up to 120 hours post-dose to measure plasma Maraviroc and metabolite UK-463,977 concentrations and radioactivity and for metabolite profiling, respectively. Urine and feces were collected to measure urinary and fecal radioactivity and for metabolite profiling up to at least 120 hours post-dose on day 1. UK-463,977 concentrations were also determined in urine. Unchanged Maraviroc was the main circulating component in plasma (42% of plasma radioactivity), and the metabolites UK-408,027 (22%), an amine analogue (11%) and UK-463,977 were also identified in plasma. The metabolites UK-408,027 or UK463,977 appear not to accumulate with time.

Maraviroc achieves concentrations within the EC90 range in CSF and showed viral suppression in CSF. The CSF:plasma ratio of Maraviroc was reported as 0.03 (0.01–0.10) ^27,28^.

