**Adverse events (AEs):** AEs were similar in frequency and character in patients treated with Maraviroc or placebo and were expected in this treatment population. Furthermore, no relevant differences in AEs (including serious AE) were seen in Maraviroc given QD versus BID. Infections (upper respiratory and herpes simplex) were somewhat more common with Maraviroc than with placebo, also after adjustment of exposure. Herpes simplex as a manifestation of immune response inflammatory syndrome (IRIS) is a well-known phenomenon and could be one possible explanation for this particular finding. AIDS-related infections and malignancies were not more common with Maraviroc, and autoimmune disorders were not reported. No major safety concerns were found with Maraviroc as part of the antiretroviral regimen in treatment-experienced patients. The dose-limiting adverse event, postural hypotension, appeared to be clinically manageable with the chosen dosage of 300 mg. Maraviroc was well tolerated, with the same frequency of study-drug discontinuation for Maraviroc and placebo. The spectrum of AEs reported, including serious AEs and deaths, did not reveal any specific issues considering the population studied. The frequency of liver-related AEs does not raise any concerns for liver toxicity. In late 2004, four large studies were initiated (phase IIb and phase 3), with 4794 patients screened at more than 200 sites in the United States, Canada, Europe, Australia, South Africa, Mexico and Argentina. An in-depth review of all data for evidence of hepatotoxicity for MVC and a high level of vigilance for any signals did not find any evidence for a systematic increase in hepatic enzymes or other markers for hepatotoxicity. Shortly afterward, concerns were raised regarding a potential increased risk for certain malignancies, and initially, there were concerns that this could be a class effect based on the immune-modulatory potential of CCR5 antagonists, but review of data from other vicriviroc studies, as well as the MVC studies, did not support this theory.^32^

Maraviroc (150 mg and 300 mg BID) received approval for use in the United States in August 2007 and in the European Union in September 2007.

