# This study will evaluate the safety and efficacy of Maraviroc 300 mg per day in patients suffering from PSD.

Primary objective:

1. To investigate the safety and tolerability of Maraviroc 300 mg per day in subjects with PSD.

Secondary Objectives:

1. To investigate the safety and tolerability of Maraviroc 300 mg in PSD subjects, with special attention to: effects on heart rate and blood pressure.
2. To evaluate the efficacy of Maraviroc 300 mg per day in improving depressive symptoms in subjects with PSD, as assessed by a change from baseline in the Montgomery-Asberg Depression Rating Scale (MADRS) total score and in improving cognitive, functional, and behavioral outcomes.

To evaluate the effect of treatment with Maraviroc 300 mg per day for 10 weeks on blood inflammatory markers in subjects with PSD.

3. To assess the effect of Maraviroc 300 mg in PSD subjects on: a. Depressive symptoms, as assessed by the 16-item Quick Inventory of Depressive Symptomatology- Self Report (QIDS-SR16) b. Remission, defined as a MADRS total score ≤10 c. Response, defined as a ≥50% reduction from baseline in MADRS total score d. The severity of illness using the Clinical Global Impression - Severity (CGI-S) and the Patient Global Impression - Severity (PGI-S) e. Symptoms of anxiety as assessed by the Generalized Anxiety Disorder 7-item Scale (GAD-7). d. Cognitive status, as assessed by cognitive score based on repeatable computerized battery of cognitive tests (Neurotrax) and Montreal Cognitive Assessment (MoCA). e. Functional outcome, as assessed by the stroke impact scale (SIS), the activities of daily living (ADL) score, and Reintegration to Normal Living Index (RNL).

Methods

We plan to enroll ten adults with PSD.

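### The 2-hour first-dose window reaches peak concentration on only one of two conflicting Tmax statements, and no planned blood-pressure reading is specified as postural

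*Protocol*

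**What the plan says.** **First dose.** Recruitment and retention plans: "During the first administration, participants will remain under clinical supervision and vital signs monitoring for 2 h". The next sentence adds: "Blood pressure and heart rate will be recorded before discharge". The drug is given once the baseline assessments are complete.

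**Time to peak.** The opening of Toxicology states: "At a single dose of 150 mg or 300 mg, time to maximum concentration occurred by 2 hours post-treatment in humans". The Absorption paragraph under Clinical aspects states: "The mean Tmax was between 2 and 3 hours with individual values ranging from 0.5 to 8 hours (with food". It also describes absorption as very variable, with more than one peak.

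**The effect of interest.** The Adverse events paragraph under Clinical safety says: "The dose-limiting adverse event, postural hypotension, appeared to be clinically manageable with the chosen dosage of 300 mg". Toxicology links orthostatic hypotension to doses of 600 mg or more. It also reports a recommendation that users of antihypertensives be asked about orthostatic symptoms. Secondary objective 1 concerns safety and tolerability, "with special attention to: effects on heart rate and blood pressure".

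**Measurement.** Table S1 marks vital signs at screening, Day 1 and weeks 2, 4, 7 and 10. Supplementary Figure S1 and the follow-up list after Table S1 also name them at weeks 14 and 18, after treatment has stopped. None of these places states posture. On daily dosing, the Protocol says: "Participants will take Maraviroc 300 mg at 6-8AM". It does not ask for the time between dose and reading.

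**The concern.** There are two separate problems.

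The first is an internal conflict. A 2-hour observation period fits a drug that peaks by 2 hours. It fits less well if the average peak falls between 2 and 3 hours and some patients peak much later. The Protocol states both and does not say which one the window rests on.

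The second is a gap between objective and measurement. A postural fall in blood pressure is a difference between lying and standing. A protocol that asks only for vital signs, or for blood pressure and heart rate, can be followed to the letter with seated readings. At the later visits those readings may also fall at any unrecorded interval after the dose.

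Safety is the primary objective, there are 10 patients and there is no control arm. A report of no blood-pressure effect would inform the later dosage research that the Design section foresees. If the readings could not have shown a postural effect, that report would be weak evidence on the one event the Protocol calls dose-limiting.

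**Working it through.** The Protocol derives no figure on this point, so there is none to reproduce. The check sets its statements side by side.

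**Step 1: window against Tmax.** Inputs: window 2 h (Recruitment and retention plans); Tmax by 2 h at 150 or 300 mg (Toxicology); mean Tmax 2 to 3 h and individual values 0.5 to 8 h with food (Absorption). Shortfall = Tmax − window.

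| Statement used | Calculation | Shortfall |
|---|---|---|
| Toxicology, latest value | 2 − 2 | 0 h |
| Absorption, lower end of mean | 2 − 2 | 0 h |
| Absorption, upper end of mean | 3 − 2 | 1 h |
| Absorption, latest individual value | 8 − 2 | 6 h |

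**Step 2: illustration of how many patients would peak after 2 h if the Absorption figures apply.** Assume Tmax is lognormal with mean m. Take the log range ln 8 − ln 0.5 = ln 16 = 2.773 as ±2 or ±3 standard deviations. Then σ = 2.773/4 = 0.693 or 2.773/6 = 0.462. With μ = ln m − σ²/2, P(Tmax > 2) = 1 − Φ((ln 2 − μ)/σ).

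| m | σ = 0.693 | σ = 0.462 |
|---|---|---|
| 2 h | 0.364 | 0.409 |
| 2.5 h | 0.490 | 0.599 |
| 3 h | 0.594 | 0.741 |

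That is about 4 to 7 of 10 patients. The distribution and σ are assumptions, not Protocol figures. If the Toxicology statement applies, the number is 0.

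**Step 3: what is specified for each reading on drug.**

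| Reading | Posture stated | Tied to dose |
|---|---|---|
| Day 1, before dose | No | Yes, drug follows assessments |
| Day 1, monitoring and discharge | No | Yes, within the 2-h stay; number of readings not stated |
| Weeks 2, 4, 7, 10 | No | No |

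If visit-day doses follow the 6 to 8 AM instruction, a reading at a known clock time still leaves time since dose uncertain by 8 − 6 = 2 h. That is as long as the whole first-dose window. Table S1 also marks drug administration at these visits, so where and when the visit-day dose is taken is itself not settled.

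**Step 4: symptom questioning.** Toxicology names rash, fever, aches, blisters and facial swelling for the calls, in an open-ended list. The orthostatic question appears there only as a reported recommendation. The Interventions section mentions a script and checklist for the calls but does not give their content.

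**The case against.** The strongest case for the plan is that the Toxicology statement is the one given explicitly for the trial's dose, and the 2-hour window matches it. The Absorption paragraph names no dose for its mean, and its range carries a food condition. The two might be reconciled if they come from different doses or feeding states. The Protocol also links orthostatic hypotension to 600 mg or more, calls it manageable at 300 mg, and reports orthostatic symptoms in 8% of both active and placebo patients in a large trial. It nowhere says that the blood-pressure effect peaks at Tmax. Adverse events are recorded at every visit and call after screening, so symptomatic hypotension should surface.

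Much of this stands. It lowers the expected frequency of the event and leaves open which Tmax figure applies. It does not remove the conflict: no dose or feeding condition is given that would reconcile the figures, and no feeding condition is stated for the first dose. Nor does it supply a postural measurement, and a drop without symptoms would not be reported as an adverse event.

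A reader might also infer more than the text supports:

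- That Day 1 has a single reading. The text describes monitoring over 2 hours plus a recording before discharge; the number is unstated.
- That no reading is timed to dose. Day 1 is anchored to it.
- That later readings are taken at arbitrary clinic hours, or that the Day 1 dose cannot fall between 6 and 8 AM. No clinic hours are given.

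**Conclusion.** The point holds in two limited parts.

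1. The Toxicology and Absorption statements on Tmax conflict, and the first-dose window depends on which applies. The shortfall is nil on one. On the other it is 0 to 1 hour against the mean and up to 6 hours against the latest individual value. A reader might conclude that Day 1 monitoring does not cover peak exposure. The documents do not support that, because it would settle the conflict in favour of the Absorption paragraph.

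2. Postural hypotension is singled out as dose-limiting, and blood pressure and heart rate are a stated focus. Yet posture is unspecified at every reading, and time since dose is unspecified at weeks 2, 4, 7 and 10. This part stands whichever Tmax figure is right. It rests on the absence of any lying or standing instruction in the text, not on an assumed event rate.

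This is an inexpensive improvement that the sponsor should make. It does not show that the trial is unsafe or that an effect will be missed.

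**What to change.** - Reconcile the Toxicology and Absorption statements on Tmax, giving the dose and feeding condition behind each. State which one the supervision window in Recruitment and retention plans rests on. The length of supervision is the sponsor's decision.
- In Table S1, define vital signs as lying and standing blood pressure and heart rate at the readings already planned, including the Day 1 reading before dosing, so that postural change has a baseline.
- Record the clock time of that day's dose and of each reading.
- Carry the orthostatic-symptom question reported in Toxicology onto the existing phone checklist, if it is not already there.

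The cost is a few extra minutes per visit, two clock-time fields and one checklist line. No visit is added.
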